**Figure 2 F2:**
[figure not shown]
Triangle of Petit landmarks are identified through the same abdominal incision used to harvest the abdominal flap.

#### Intraoperative analgesic protocol

Intraoperatively, fentanyl in aliquots of 1 μg/kg will be administered for pain control, in addition to an induction dose of 3 μg/kg. Upon completion of the surgery, each patient will receive a dose of 50 to 100 mg of indomethacin and 1,300 mg of acetaminophen per rectum. In addition, ketorolac will not be given intraoperatively. Dexamethasone (4 mg) will be administered in the operating room (OR) for all patients to prevent postoperative nausea and vomiting.

#### Intermittent transversus abdominis plane block protocol

At the conclusion of surgery, a 0.2 ml/kg bolus of 0.25% bupivacaine or saline solution will be injected through each catheter in the OR. At midnight following the operation, 0.2 ml/kg of 0.25% bupivacaine or saline will be injected through each catheter every 8 hours for the next 2 postoperative days by a member of the pain service. At 8 AM on postoperative day 3, the TAP catheters will be removed by the pain team (Figure 3).

**Figure 3 F3:**

**Intermittent bolus injection diagram.** OR, operating room; POD, postoperative day.

#### Local anesthetic toxicity

For a 70-kg female undergoing bilateral breast reconstruction, the use of 0.2 ml/kg of 0.25% bupivacaine in each TAP catheter every 8 hours in the study group will result in a 1 mg/kg dosage bupivacaine ((0.2 ml/kg × 70 kg × 2 sides = 28 ml) (70 mg × 0.25% concentration = 70 mg)). Because the maximum recommended dosage of bupivacaine over 6 hours is 2.5 to 3.0 mg/kg, our prescribed dosing protocol every 8 hours is well below the toxic range.

#### Postoperative treatment

Each patient will receive intravenous hydromorphone through a PCA pump programmed for demand-only mode with no basal rate. PCA will be set at 0.1 mg per bolus every 5 minutes as needed (to a maximum of 10 mg per 4 hours), which will be initiated in the recovery room. The PCA will be filled with hydromorphone as per standard care at our institution. When patients can tolerate liquids, they will be given 1 g of plain acetaminophen every 6 hours around the clock. Once the PCA is discontinued, patients will be offered 5 to 10 mg of oxycodone every 2 to 4 hours as required, in addition to 1 g of acetaminophen every 6 hours around the clock. Granisetron (1 mg every 12 hours will be the first-line therapy for postoperative nausea and vomiting. Patients will be encouraged to ambulate on postoperative day 1. A liquid diet, then a solid diet, will be offered on postoperative day 1 and advanced as tolerated. The PCA system will be discontinued at 8 AM on postoperative day 3.

### Primary end point and secondary end points

The primary end point evaluated will be the mean postoperative opioid consumption in the first 2 postoperative days. Both intravenous PCA opioids and oral opioids will be recorded from the patients’ medical records daily. All opioid doses will be converted to intravenous morphine equivalent units for comparison.

The secondary outcomes of interest will include the following. The continuous outcomes will be total in-hospital cumulative opioid consumption, total in-hospital cumulative antinausea medication consumption, score on the Quality of Recovery (QoR) questionnaire administered once on postoperative day 4 (scored from 0 to 18, with a greater score indicating better QoR) [9] and duration of hospital stay. Therepeated-measures outcomes will be assessed by recording daily pain intensity scores at rest and with movement measured using a Visual Analogue Scale for pain (scored from 0 to 10, with 0 indicating no pain and 10 indicating worst pain ever), postoperative nausea and vomiting (scored from 0 to 3) and sedation score. The time to event outcomes will be recorded for time to first postoperative bowel movement and time to ambulation.

The data extraction forms will be completed prospectively by a member of the pain team.

### Data analysis

Patients who have major postoperative complications that require a second surgery, such as evacuation of a hematoma or microsurgical revision, will not be removed from the study and will be evaluated using the intention-to-treat analysis. An initial examination will be performed to detect any differences between the two treatment groups despite the randomization. Patients’ clinical, surgical and oncological characteristics, such as BMI and method of reconstruction (DIEP or MS-TRAM) will be collected and their association with the primary and secondary outcomes will be tested in univariate analysis models to detect possible confounding factors. The effect of treatment groups will be studied next using an appropriate multivariate analysis model for each outcome while controlling for the possible confounding factors, if indicated, such as BMI and method of reconstruction. All statistical analyses will be performed using SAS software version 9.2 (SAS Inc, Cary, NC, USA). All tests will be two-sided, and significance will be set at *P* < 0.05.

The primary analysis will comprise mean postoperative opioid consumption during the first 48 hours postoperatively, which will be reported for the two groups as means (±SD). The two groups will be compared using the two-sample Student’s *t*-test or the Wilcoxon rank-sum test, depending on the results of the normality test. The secondary analysis will assess continuous outcomes, which will be reported for the two groups as means (±SD). The median and range will also be reported. The two groups will be compared using the two-sample Student’s *t*-test or the Wilcoxon rank-sum test, depending on the normality test.

Repeated-measures outcomes will be analysed to assess the effect of treatment (between-subject variable), time (within-subject variable) and a possible treatment × time interaction on outcomes measured at various time points. Time-to-event outcomes will be measured from the completion of surgery until the time of the event. Patients who do not experience the event at the time of the last follow-up will be censored. The number of censored events is expected to be low because both events (ambulation and bowel movement) are required to occur prior to the patient’s discharge from the hospital. Time-to-event outcomes will be analysed using the Kaplan-Meier method, and survival curves will be compared between the two groups using the logrank test.

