### Randomization

Once informed consent is obtained from the patient to participate in this trial, the research assistant will contact the study pharmacist to obtain the patient’s randomization arm. Patients will be randomized to receive either bupivacaine (study group) or isotonic saline (control group) through the TAP catheter by intermittent injection. The randomization allocation list will be developed by the Department of Epidemiology and Biostatistics at the University Health Network Research Institute. Randomization allocation will be equal between the study groups and stratified by laterality of abdominal flap harvest (unilateral vs. bilateral) and the timing of breast reconstruction (at the same time as mastectomy (immediate) vs. at a later time, after the mastectomy (delayed)). Sequentially numbered and sealed envelopes containing the treatment assignments will be prepared and given to the study pharmacist. The patient, surgeon, research assistant and all other study personnel will be blinded to randomization. The randomization code will be revealed only after the completion of the trial and all the patient data have been collected.

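### The primary test leaves out the two randomisation strata, and the follow-up model includes them only if outcome-based screening selects them

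*Protocol article*

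**What the plan says.** The Randomization section of the protocol article states that allocation is "stratified by laterality of abdominal flap harvest (unilateral vs. bilateral) and the timing of breast reconstruction", which gives four strata.

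The Data analysis section compares 48-hour opioid consumption between groups with a two-sample t-test or the "Wilcoxon rank-sum test, depending on the results of the normality test". It names no stratum or covariate for this comparison. The Sample size calculations section also assumes an unstratified rank-sum test.

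The same Data analysis section sets out a separate route to adjustment:
- Balance is checked first: "An initial examination will be performed to detect any differences between the two treatment groups despite the randomization".
- Patient characteristics are then screened: "their association with the primary and secondary outcomes will be tested in univariate analysis models to detect possible confounding factors".
- Every outcome, the primary one included, then gets a second treatment comparison from a multivariable model, fitted "while controlling for the possible confounding factors, if indicated, such as BMI and method of reconstruction".

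The two named examples, BMI and flap type, are not stratification factors. Laterality and timing are named nowhere in the analysis text. The logrank tests for bowel movement and ambulation are also described without strata.

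**The concern.** Stratified allocation balances the groups on the strata, so the treatment difference varies less from trial to trial than under simple randomisation. A test that ignores the strata still counts between-stratum variation as noise. If the strata are prognostic, its standard error is too large, it rejects too rarely under the null, and it gives up the precision that stratification provided.

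The multivariable model does not reliably repair this. Its covariates depend on tests against the outcome in this trial, so laterality and timing enter only if they happen to be selected. Design factors belong in the model whatever their observed P value.

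This is not a detail left to a statistical analysis plan. The article itself fixes the unstratified test and the screening strategy.

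**Working it through.** **1. The plan's own figure.** Inputs from Sample size calculations: 9.2 vs 4.6 mg, SD 5.8 mg, two-sided alpha 0.05, power 80%, rank-sum test, normal data. Noether's formula:

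- p = Φ(4.6 / (5.8 × √2)) = Φ(0.561) = 0.7125
- N = (1.960 + 0.842)² / (12 × 0.25 × (0.7125 − 0.5)²) = 57.9, or 29 per group

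The stated 29 per group reproduces. It uses the full SD, with no reduction for strata.

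**2. Size of the conservatism.** Let R² be the share of within-group outcome variance explained by the strata. The documents do not give it, so 0 to 30% is assumed. With n per group and exact balance within strata, the treatment difference has variance 2σ²(1 − R²)/n, while the unadjusted test uses about 2σ²/n. True type I error is therefore about P(|Z| > 1.96/√(1 − R²)):

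- R² = 10%: cut-off 2.07, error 3.9%
- R² = 20%: cut-off 2.19, error 2.8%
- R² = 30%: cut-off 2.34, error 1.9%

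**3. Simulation at 29 per group.** The document's effect and SD were used with normal data. The other settings are assumptions: permuted blocks of 4 within four strata, stratum factor prevalences of 35% and 50%, and six candidate covariates screened at P < 0.05. There were 5,000 null and 3,000 alternative runs per setting.

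| Strata R² | Null: planned test | Null: screened model, strata not among candidates | Null: treatment + strata | Power: planned | Power: treatment + strata |
|---|---|---|---|---|---|
| 0% | 5.0% | 4.9% | 5.0% | 84% | 84% |
| 10% | 4.5% | 4.1% | 5.5% | 85% | 87% |
| 20% | 2.9% | 2.9% | 4.7% | 86% | 91% |
| 30% | 2.4% | 2.4% | 5.1% | 87% | 95% |

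From the unrounded results, the power gain is about 0, 2, 5 and 7 points. Two further simulations with their own assumed strata gave null rejection of 3.6, 2.6 and 2.0%, and of 4.0, 2.6 and 2.7%, at R² of 10, 20 and 30%. Across all of these the range is about 2 to 4.5%.

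**4. At 86 patients.** The Trial status section reports 86 enrolled. With the same effect and SD, power is about 95 to 97% unadjusted and 95 to 99% adjusted, a gain of about 0 to 2 points.

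**5. Which adjusted analysis.** The Background section reports the group's earlier 48-hour PCA use as 48.44 ± 39.53 mg and 17.10 ± 17.23 mg. The coefficients of variation are 39.53/48.44 = 0.82 and 17.23/17.10 = 1.01, which suggests marked right skew. Simulated lognormal data (58 patients, 50% reduction, strata explaining 0, 10, 20 and 30% of log-scale variance; all assumed except the CV of 0.82) gave this power:

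| CV | Planned rank-sum | Raw-scale linear model with strata |
|---|---|---|
| 0.82 | 94, 94, 96, 97% | 90, 90, 94, 96% |
| 1.0 | 87, 87, 87, 89% | 77, 80, 82, 85% |

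A separate run at CV 1.0 agreed, with 85 to 89% against 76 to 86%. In that run a log-scale model or a van Elteren test kept or improved power once the strata were prognostic. The van Elteren test lost up to about 2 points if they were not.

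**The case against.** The strongest reply is that the planned test is safe. It does not exceed 5% under the null, and its power stays above the planned 80%. The benefit of adjustment rests on a prognostic strength that the documents never give, and it shrinks to 0 to 2 points at 86 patients. Laterality and timing could also count as surgical characteristics in the open list of candidates. All of this stands, and it limits the point to one of efficiency and clarity. It does not remove the point, because entry through screening remains conditional and including the strata costs almost nothing.

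A reader might infer more than the documents support:

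- **That two treatment P values inflate the type I error materially.** The Data analysis section labels the unadjusted comparison as primary, and the sample size rests on the same kind of test. What is missing is a statement that the adjusted model is supportive. If success were claimed on either result, the simulation in step 3 adds only about 0.4 to 1.2 points over the unadjusted test alone: 5.4% against 5.0% with nothing prognostic, and 4.3% against 3.1% with strata and covariates each explaining 20%. A run with 12 candidate covariates, 3 of them prognostic, reached 6.9%, but the article names only two examples.
- **That the strata were chosen because they drive opioid need.** The Randomization section gives no reason for choosing them.
- **That baseline significance testing is planned.** The text describes an examination for differences and does not name a test.
- **That any linear model would be better.** On data as skewed as the group's own, a raw-scale model is weaker than the planned rank-sum test.

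**Conclusion.** The point holds as a modest one that should be corrected. Randomisation is stratified, the primary test is not, and the only adjustment offered depends on outcome-based screening that may leave the strata out. If the strata explain 10 to 30% of outcome variance, the primary test runs at about 2 to 4.5% instead of 5% and gives up about 2 to 7 points of power at 58 patients. These sizes assume normal data, stratum proportions that the documents do not give, and near balance within strata. If the strata explain nothing there is no material gain. The stated power is met in every normal-data setting examined, so the plan should not be described as underpowered or as inflating false positives.

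**What to change.** Prespecify one primary analysis that includes laterality and timing and suits skewed data. Either option serves:

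- a linear model of log-transformed (or otherwise suitably transformed) 48-hour consumption on treatment, laterality and timing, plus BMI and flap type if these are named in advance, with a stated rule for any zero values; or
- a van Elteren test stratified by the two factors, if a rank analysis is preferred.

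Replace the univariate outcome screening with this fixed covariate set, use it for the secondary models, and stratify the logrank tests by the same two factors. State that the unadjusted comparison is supportive.

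The cost is wording and a few degrees of freedom. At 58 patients, a model with treatment and four covariates leaves 58 − 6 = 52 residual degrees of freedom, against 56 for the t-test. The van Elteren option may lose up to about 2 points of power if the strata are not prognostic. No new data are needed: the strata are known at randomisation, and BMI and flap type are already to be collected. The article keeps the code concealed until all data are in and reports enrolment still open, so at its date the change could be made blind.

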### Sample size calculations

A retrospective review of 45 patients matched on key characteristics that underwent free MS-TRAM or DIEP breast reconstruction between January 2009 and March 2010 prior to the use of TAP block revealed a mean total opioid consumption of 9.2 mg ± 5.8 mg of intravenous morphine equivalent per patient. Using these preliminary data, we will require 29 patients per group to achieve 80% power to detect a 50% reduction in mean total opioid consumption between the control and study groups (9.2 vs. 4.6 mg, respectively) with group standard deviations of 5.8 mg and a significance level (Cronbach’s α) of 0.05 using a two-sided Wilcoxon rank-sum test assuming that the actual distribution is normal. From January to December 2010, approximately 100 patients underwent microsurgical breast reconstruction using abdominal tissue performed by the two participating surgeons (TZ and [name]). It is anticipated that approximately 80% of these patients will be eligible and willing to participate in the study (approximately six or seven patients per month). A total of 58 patients will be enrolled into this proposed study, thus the estimated accrual time is approximately 9 to 12 months.

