Our group recently published the results of a prospective cohort study that compared the total intravenous *patient-controlled analgesia* (PCA) opioid consumption between a group of 45 consecutive patients who received intermittent postoperative bolus injections of 0.25% bupivacaine through the TAP catheter and a group of 80 historic control patients who underwent the same abdominally based microsurgical breast reconstruction without TAP blocks [25]. We found that the 48-hour PCA-delivered opioid requirement was significantly less (*P* < 0.001) in the TAP block group (17.10 ± 17.23 mg intravenous morphine equivalent) compared to the control group (48.44 ± 39.53 mg). Although we concluded on the basis of data derived from our study that intermittent delivery of bupivacaine through the TAP block significantly reduced postoperative parenteral opioid requirements following abdominally based breast reconstruction, there are inherent biases associated with using historic controls. Therefore, we designed our present double-blind, placebo-controlled, randomized controlled trial (RCT) to rigorously assess the efficacy of reducing postoperative donor site pain by intermittently delivering a LA agent through the TAP catheter in patients undergoing breast reconstruction using abdominal tissue microsurgical reconstruction.

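### The planning figures of 9.2 ± 5.8 mg cannot be reconciled with the group's own 48.44 ± 39.53 mg in the same unit, so the 4.6 mg target is not shown to be on the primary endpoint's scale

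*Protocol article*

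**What the plan says.** Protocol article, Sample size calculations: a retrospective review of 45 patients treated before TAP blocks were used "revealed a mean total opioid consumption of 9.2 mg ± 5.8 mg of intravenous morphine equivalent per patient". From this, "we will require 29 patients per group to achieve 80% power to detect a 50% reduction in mean total opioid consumption", that is "9.2 vs. 4.6 mg, respectively) with group standard deviations of 5.8 mg", at a significance level "of 0.05 using a two-sided Wilcoxon rank-sum test assuming that the actual distribution is normal". The total is 58. The paragraph does not give the period over which the 9.2 mg was accumulated.

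Protocol article, Background: the group's published cohort compared 45 TAP-block patients with 80 historic controls who had the same operation without a block. The opioid delivered by PCA over 48 hours was "17.10 ± 17.23 mg intravenous morphine equivalent) compared to the control group (48.44 ± 39.53 mg").

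Protocol article, Primary end point and secondary end points, and Data analysis: the primary endpoint is PCA plus oral opioid over the first 48 hours, all converted to IV morphine equivalents.

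**The concern.** Both control figures come from patients who had abdominally based microsurgical breast reconstruction without a TAP block, and both carry the same unit label. The planning figure is called a total. The cohort figure counts PCA only. In comparable patients over the same window, a total cannot be a fifth of one of its own parts. The assumed control mean of 9.2 mg is even below the cohort's mean with the block, 17.10 mg.

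At stake is the benchmark for reading the result. The 4.6 mg is the only target difference the article states in milligrams. If the endpoint is really on the cohort's scale, 4.6 mg is about a tenth of the control mean and not half of it. The SD and the power claim rest on the same unreconciled source.

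**Working it through.** **Inputs.** From Sample size calculations: control 9.2 mg, target 4.6 mg, common SD 5.8 mg, two-sided alpha 0.05, power 80%, Wilcoxon test on normal data, 29 per group. From Randomization: equal allocation. From Background: controls 48.44 ± 39.53 mg, TAP block 17.10 ± 17.23 mg. From Trial status: 86 enrolled.

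**1. The plan's own figure.** Standardised difference d = 4.6/5.8 = 0.793.
- Normal approximation: n = 2(1.960 + 0.842)²/0.793² = 25 per group.
- Two-sample t-test: 25.95, so 26.
- Wilcoxon, dividing by the asymptotic relative efficiency 3/π = 0.955: 27.2, so 28.
- Power at 29 per group: 84.3% (t-test) and 82.6% (Wilcoxon approximation); simulated Wilcoxon power is 81.7%.

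The stated 29 is reproduced to within one patient. The arithmetic is sound for its inputs.

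**2. The two control figures side by side.**

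| | Sample size section | Background controls | Ratio |
|---|---|---|---|
| Mean, mg | 9.2 | 48.44 | 5.27 |
| SD, mg | 5.8 | 39.53 | 6.82 |
| CV | 0.63 | 0.82 | |
| Opioid counted | total | PCA only | |
| Window | not stated | 48 h | |

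A unit or conversion error by one constant would multiply mean and SD alike and leave the CV unchanged. The mean needs a factor of 5.27 and the SD 6.82, so one factor does not reproduce both.

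**3. Chance.** Treating the samples as independent, the difference is 48.44 − 9.2 = 39.24 mg and its standard error is √(39.53²/80 + 5.8²/45) = 4.50 mg. That is 8.7 standard errors.

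**4. Could the 45 be a subset of the 80, on the same scale?** The other 35 would then average (80 × 48.44 − 45 × 9.2)/35 = 98.9 mg. The between-subset sum of squares would be 45 × 39.24² + 35 × 50.45² ≈ 158,400. The total sum of squares for all 80 is only 79 × 39.53² = 123,447, so this is impossible.

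**5. The target on the cohort's scale.** 4.6/48.44 = 9.5% of the control mean. A 50% reduction there is 48.44/2 = 24.22 mg.

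**6. Power for a 50% reduction at 29 per group, on cohort figures.**

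| SD assumption | d | t-test | Wilcoxon (3/π) |
|---|---|---|---|
| Arm-specific, 39.53 and 17.23 (root mean square 30.49) | 0.794 | 84.4% | 82.7% |
| Equal CV in both arms, 39.53 and 19.77 | 0.775 | 82.6% | 80.8% |
| Control SD 39.53 in both arms | 0.613 | 63.0% | 61.0% |
| Plan's figures times any constant | 0.793 | 84.3% | 82.6% |

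In the third row, 80% power needs 43 (t-test) or 45 (Wilcoxon) per group. If the 86 enrolled split equally, 43 per group gives 80.2% or 78.3% in that row, and about 95% in the first row. The Wilcoxon column carries the normal, equal-variance efficiency over to the unequal-SD rows and is approximate there.

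**The case against.** The strongest reply is that power depends only on the ratio of difference to SD. A constant unit error would leave N and power untouched and make this a labelling matter. Most cohort-based scenarios for a 50% reduction also reach 80%. The low one puts the control SD into both arms although the Background gives 17.23 mg for the TAP arm. With the cohort's observed difference of 48.44 − 17.10 = 31.34 mg, even that SD gives d = 0.793 and power of 83 to 84%. All of this stands. It answers a claim of low power, but it leaves the milligram figures unexplained.

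The comparability of the two samples can also be questioned. The 45 were matched on characteristics the article does not list, the centre of the two historical samples is inferred, and their windows may differ. That is fair, and it is why the cause must remain open. But if window or population explains the gap, the planning figures do not describe the 48-hour endpoint, which is the same problem.

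Three stronger readings are tempting, and the documents do not support them:
- **The trial is underpowered.** The 61 to 63% needs one particular SD assumption, and the article's own arm-specific SDs contradict it.
- **Power is about 7%.** This comes from setting 4.6 mg against 39.53 mg (d = 0.116). It mixes two scales; the plan targets a 50% reduction.
- **The 9.2 mg is unconverted hydromorphone.** A reader might infer this from the trial's PCA drug. The article gives no conversion factor and does not name the drug in the 45-patient review, and no single factor fits both mean and SD. Nor is there evidence that the endpoint itself will go unconverted: the endpoint section says all doses will be converted.

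**Conclusion.** The concern holds as an unexplained inconsistency in the planning inputs. Under one unit label, the control mean differs 5.3-fold and the SD 6.8-fold between two sections of the same article. The direction is opposite to what a total against PCA alone should give. Chance does not explain it if the samples are independent, and a same-scale subset is ruled out. Unit, conversion, window and population remain possible causes, alone or together, and the article does not say which applies.

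The 4.6 mg target and the 5.8 mg SD are therefore not shown to be on the primary endpoint's scale. The 80% power is not shown to be wrong. At 29 per group and a 50% reduction, it runs from about 61% (control SD in both arms) to about 83 to 84% (arm-specific SDs, or a constant unit error). These figures assume that the cohort's PCA-only spread is a fair guide to PCA plus oral opioid.

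**What to change.** Go back to the 45-patient review and state its unit, its time window and which opioids were counted. Explain how it relates to the 48.44 ± 39.53 mg in the Background, or correct it. Then restate the control mean, the SD in each arm, the target difference and the resulting power as 48-hour PCA plus oral opioid in IV morphine equivalents. Do this for the N actually targeted: Trial status reports 86 enrolled against 58 planned, and no revised calculation is shown.

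The cost is a chart re-check and a corrected paragraph. The endpoint and the test do not change and no extra patients are needed. The downside is that the restated power may be less favourable than 80%.
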